### Intervention Evaluation

#### Overview

An RCT to evaluate LiveWell has been carried out, and data analysis is underway for the following: aim (1) to establish the capacity of LiveWell to reduce relapse and symptom burden and improve QOL in bipolar disorder, aim (2) to investigate the impact of LiveWell on proximal behavioral targets and the relationship between changes in these targets and changes in relapse rate and symptom burden, and aim (3) to identify novel behavioral signatures in individuals with bipolar disorder that predict treatment response and relapse. Aim 1 will test the following hypotheses: primary hypothesis—participants in the intervention group will experience (H1) a longer time to relapse relative to treatment as usual (TAU); secondary hypotheses—participants in the intervention group will experience (H2) a lower percentage of time being symptomatic, (H3) lower symptom severity, and (H4) a better QOL relative to TAU. Aim 2 will test the following additional hypotheses: primary hypothesis—participants in the intervention group will experience (H1) larger improvements in proximal behavioral targets (eg, medication adherence) relative to TAU; secondary hypotheses—variation in the proximal behavioral targets will account for substantial variance in the (H2) primary clinical outcome (time to relapse) and secondary clinical outcomes of (H3) percentage time symptomatic and (H4) symptom severity; proximal behavioral targets will mediate the intervention effect on the (H5) primary clinical outcome (time to relapse) and the secondary clinical outcomes of (H6) percentage time symptomatic and (H7) symptom severity; tertiary hypotheses—participants in the intervention group will experience (H8) an increase in performance determinant scores for each target, and at the final time point, will have (H9) higher performance determinant scores for each target relative to TAU. Aim 3 is exploratory and will develop a database of behavioral sensing (intervention and TAU arms) as well as app use and self-assessment (intervention arm only) data. The relationships between these data and clinical status assessment data will be examined with the long-term goal of better predicting current relapse risk, treatment response, and longitudinal course for individuals with bipolar disorder.

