#### Outcome and Target Assessment Delivery

Assessors blinded to the study arm conducted outcome and target assessments by telephone at baseline and then every 8 weeks until study exit at week 48 (Figure 6). Windows for complete assessments were up to 4 weeks after the assessment due date, calculated from the baseline assessment date. To minimize assessment burden and because QOL may vary less rapidly than other outcomes [172], the QOL assessment was delivered only at 0, 24, and 48 weeks. Assessments began by focusing on participants’ experiences over the prior 2 weeks. Mood and sleep were assessed using combined mood (CMF, QIDS, and Young Mania Rating Scale) and combined sleep (CMF, QIDS, and Pittsburgh Sleep Quality Index) instruments (Multimedia Appendix 7). The combined instruments streamlined the interviews and reduced the time required to complete the assessments. This was followed by assessment during the prior 2 weeks of routine (Social Rhythm Metric), medication adherence (Tablet Routine Questionnaire), and depending on the week QOL.

Information from the assessment of the prior 2 weeks was then used to anchor the timeline follow-back of weekly depressive and manic symptom severity (LIFE-CMF). In addition to assessing symptom severity, timeline follow-back using the LIFE assessed weekly variations in anxiety, suicidal ideation and attempts, psychotic symptoms, substance use, life events [173], mental health treatment attendance, and psychiatric medication adherence (Multimedia Appendix 7). The Symptom Management Scale was assessed last because it did not focus on experiences during the previous 2 weeks or since the last assessment. Instead, participants were asked to imagine experiencing ongoing or new low-level depressive or manic symptoms and how they might manage them (Multimedia Appendix 7). This approach was used because participant clinical status during the assessment interval may not have required management of prodromal or residual symptoms.

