#### Analysis Overview

As the randomization was stratified by risk group, analyses will examine if an interaction between risk strata and the study arm is present. If no evidence of an interaction is evident, the models will be stratified or adjusted for risk strata. For time to relapse, missing data for participants who dropped out or were lost to follow-up will be censored at their last study visit. Percentage time symptomatic will be calculated based only on the observed time in the study. For longitudinal data (symptom severity, QOL, targets), multiple imputation using Markov Chain Monte Carlo methods will be used to address missing data by creating five unique data sets (SAS procedure PROC MI), and the results will be combined (SAS procedure PROC MIANALYZE) to obtain valid statistical inferences and least square means of the outcomes for each time point data will be calculated.

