#### Aim 1: Primary and Secondary Outcomes Analysis

Time-to-relapse curves will be constructed using the Kaplan-Meier method. Log-rank tests will be used to determine if there is a univariate impact of the study arm while adjusting for risk strata. Cox proportional hazard models will then be fit to adjust for risk strata. Proportional hazards assumptions will be assessed, and the estimated hazard ratio and CIs will be presented. To compare percent time symptomatic, linear regression models will be used to determine if there was an interaction between risk strata and the study arm. If no evidence of interaction is seen, the main effect of arm will be reported and least square means will be estimated while adjusting for risk strata. Generalized linear mixed models for longitudinal data will be used for symptom severity and QOL measures. We will examine the interactive effects of the intervention on time. If no interaction is detected, we will test the independent effects of time as well as the treatment group.

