#### Aim 2: Target Analysis

Generalized linear mixed models will be used to examine the effects of time, risk strata, and study arm on longitudinal target and determinant data. We will use the framework of Muller et al [200] to identify the targets that mediate the effect of the intervention on time to relapse, percentage time symptomatic, and symptom severity. To compare the performance determinant scores for each target at the final time point, *t* tests with correction for multiple testing between the two groups will be used.

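### Symptom severity and QOL are tested by a two-step rule with no named deciding test, so the type I error can reach about 9.75% per outcome

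*Protocol article*

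**What the plan says.** In the protocol article, Aim 1: Primary and Secondary Outcomes Analysis, the model for these outcomes is given as follows: "Generalized linear mixed models for longitudinal data will be used for symptom severity and QOL measures". The testing sequence comes next: "We will examine the interactive effects of the intervention on time", and then "If no interaction is detected, we will test the independent effects of time as well as the treatment group". The hypotheses are in Intervention Evaluation, Overview. H3 predicts lower symptom severity and H4 better QOL in the intervention arm, and neither names a visit or a contrast.

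Analysis Overview adds a separate preliminary check ("analyses will examine if an interaction between risk strata and the study arm is present") and the only stated adjustment ("If no evidence of an interaction is evident, the models will be stratified or adjusted for risk strata"). It also plans least square means at each time point.

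Outcome and Target Assessment Delivery sets assessments at baseline and every 8 weeks to week 48, so severity has seven visits, six of them post-baseline. QOL has three, two of them post-baseline: "the QOL assessment was delivered only at 0, 24, and 48 weeks". Nothing says whether the week-0 score is a covariate or part of the outcome series.

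**The concern.** H3 and H4 are statements about the difference between arms, and the rule gives each of them two openings. A significant interaction can be read as an intervention effect. If there is none, a significant arm effect can be. The result of the first test determines which quantity is reported, so the estimand for each outcome is not fixed in advance.

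A second question is what the arm main effect measures. Randomization makes the expected arm difference at week 0 zero. If week 0 sits in the outcome vector and the interaction is dropped, the arm effect averages that zero with the follow-up differences. At stake are the false-positive rate for two of the three secondary outcomes and the size and power of the effects reported for them.

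**Working it through.** **Plan's own figure.** Sample Size Considerations gives 80% power for a standardized effect of 0.43 (stated for percent time symptomatic) with 200 participants at 2:3 and 12% loss. That leaves 176, or 70.4 control and 105.6 intervention. The calculation gives 79.8% (normal) or 79.4% (noncentral t), so the figure reproduces. The article gives no error rate or power for the two-step rule.

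**Type I error.** Assumptions: each step at 5%, and either result counts as support.
- Analytic, independent steps: 1 − 0.95 × 0.95 = 9.75%.
- Simulated under no effect (10,000 runs per scenario, 80:120, correlation 0.3 to 0.7, with and without a random slope, time categorical or linear): 9.4% to 10.4% for severity and 9.4% to 10.0% for QOL. Each step alone is near 5%.

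The inflation comes from the sequence itself and would remain if the baseline score were a covariate.

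**Dilution, only if week 0 is a repeated outcome.** For a constant post-baseline effect d, the pooled arm effect is d × (post-baseline visits ÷ all visits).
- QOL: 2/3. An effect of 0.43 becomes 0.29.
- Severity: 6/7. An effect of 0.43 becomes 0.37.

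**Power under that same reading.** Assumptions: compound symmetry, unit variance, correlation ρ = 0.5, constant post-baseline effect, no gain in precision from risk strata. Let v = 1/70.4 + 1/105.6 = 0.02367, and let m be the number of post-baseline visits.

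1. Benchmark effect. The variance of the baseline-adjusted mean of the m visits is [ρ + (1 − ρ)/m − ρ²] × v. The bracket is 0.500 for QOL (m = 2) and 0.333 for severity (m = 6). For 80% power, d = 2.80 × √(bracket × v), which is 0.30 SD for QOL and 0.25 SD for severity.
2. Main-effect step. z = d × m/(m + 1) ÷ √{[ρ + (1 − ρ)/(m + 1)] × v}. This is 1.62 for QOL (power 37%) and 1.83 for severity (power 45%).
3. Interaction step. The noncentrality is d² × m/(m + 1) ÷ [(1 − ρ)v]. This is 5.23 on 2 df for QOL (power 52%) and 4.49 on 6 df for severity (power 30%).
4. Either step. The two tests are independent under compound symmetry. QOL: 1 − (1 − 0.523)(1 − 0.366) = 70%. Severity: 1 − (1 − 0.302)(1 − 0.450) = 62%.

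Over ρ from 0.3 to 0.7, with d reset to 80% each time, the combined power is 70% to 71% for QOL and 57% to 67% for severity.

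**The case against.** The strongest reply is that several parts are conditional.

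- **Baseline adjustment.** A reader might infer that the plan makes none. The article does not support that. It neither states nor excludes the baseline score as a covariate, and a condensed article may leave such detail to the analysis plan. It does state adjustment for risk strata, which are defined by clinical status at entry and so relate to baseline severity. This stands, and the dilution and power loss can only be stated conditionally.
- **Power of each step alone.** Quoting 52% and 37%, or 30% and 45%, would suggest a weaker procedure than it is, because step 1 recovers part of what step 2 loses. The combined figure is the fair one. The benchmark effects are also smaller than 0.43. At 0.43 and ρ = 0.5 the combined rule reaches about 94% for QOL and 98% for severity, even with week 0 pooled and at the inflated error.
- **Either step as success.** The article does not say that a non-directional interaction would establish a directional hypothesis. That is correct, but it also does not say that it would not, and naming the deciding test is what is missing.
- **Interest in time.** Scheduled coaching and requested daily check-ins end at week 16 while follow-up runs to week 48, so examining arm-by-time is reasonable. That justifies reporting it. It does not justify using it as a gate.
- **Aim 2.** A reader might extend the point to the behavioral targets, because H1 there predicts that "participants in the intervention group will experience (H1) larger improvements in proximal behavioral targets" while the analysis is described as "Generalized linear mixed models will be used to examine the effects of time, risk strata, and study arm on longitudinal target and determinant data". That sentence lists factors and does not rule out an arm-by-time term. It also covers determinants, which controls supply only at week 48, so it cannot be a literal model specification.

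**Conclusion.** The point holds for the two-step rule. The article fixes a data-dependent sequence for symptom severity and QOL without saying which result decides H3 or H4. Under 5% per step with either counting, the error is about 9.75% per outcome, whatever is done with baseline.

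Dilution to 2/3 (QOL) or 6/7 (severity), and combined power of about 70% or 62% where one adjusted contrast has 80%, follow only if week 0 is kept as an outcome. They also rest on a constant post-baseline effect and an assumed correlation of 0.5.

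A reader might count the arm-by-stratum check as a third route, giving 1 − 0.95³ = 14.3%. The article presents that check as a guide to handling strata, not as evidence for H3 or H4, so it is not counted here. These are secondary outcomes, and the primary time-to-relapse analysis is not touched.

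**What to change.** For each severity and QOL outcome, name one arm contrast as the test of H3 or H4, for example the arm difference averaged over post-baseline visits (weeks 8 to 48 for severity, weeks 24 and 48 for QOL). Estimate it from a model on post-baseline visits with the baseline score, visit, arm, arm-by-visit and risk stratum. Remove the interaction gate, and report arm-by-time and visit-specific differences descriptively. This returns the error to 5% per outcome and makes the role of baseline explicit.

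The cost is analysis work only, since baseline scores are already collected. One averaged contrast is less sensitive to an effect that fades or appears late, but the visit-specific estimates would still show it. The article reports that the trial has been carried out and analysis is under way. The contrast should therefore be fixed and dated before arm comparisons on these outcomes are seen. If they have already been seen, the change should be reported as made afterwards.

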#### Aim 2: Target Analysis

Generalized linear mixed models will be used to examine the effects of time, risk strata, and study arm on longitudinal target and determinant data. We will use the framework of Muller et al [200] to identify the targets that mediate the effect of the intervention on time to relapse, percentage time symptomatic, and symptom severity. To compare the performance determinant scores for each target at the final time point, *t* tests with correction for multiple testing between the two groups will be used.

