#### Outcome Assessments

The primary outcome, time to relapse, will be measured as the number of weeks to episode onset (depression, mania, hypomania, or mixed) based on the Diagnostic and Statistical Manual of Mental Disorders fourth edition (DSM-4) criteria. The DSM-4 episode criteria were chosen to allow comparison with prior RCTs of face-to-face psychotherapy for bipolar disorder, as these studies primarily used the DSM-4 episode criteria [10-18]. To determine the number of weeks to episode onset, weekly clinical status ratings (Tables 4 and 5) were assessed by timeline follow-back rating of bipolar disorder symptom severity (Multimedia Appendix 7) using a modified Longitudinal Interval Follow-Up Evaluation (LIFE) and Clinical Monitoring Form (CMF) [148,149,153]. The secondary outcomes include the percentage of time symptomatic, symptom severity, and QOL. To determine percentage of time symptomatic, weekly psychiatric status ratings (Table 6) were assessed using the LIFE-CMF to determine the percentage of time symptomatic. A week will be scored as symptomatic if the psychiatric status rating is greater than one and a half (Table 6). Symptom severity was assessed using the Quick Inventory of Depressive Symptomatology (QIDS)–Clinician Rating and the Young Mania Rating Scale [154-157]. QOL was assessed using the World Health Organization Quality of Life BREF [158].

**Table 6 table6:** Psychiatric status rating.

Score	Rating	Definition
6	Severe episode	Psychotic symptoms or severe impairment
5	Episode	No psychotic symptoms and no severe impairment
4	Marked symptoms	Symptom count^a^ >2 and marked or severe impairment
3	Moderate symptoms	Symptom count >2 or moderate impairment
2	Residual or prodromal symptoms	Symptom count >0 and ≤2. No moderate, marked, or severe impairment
1.5	Mild symptoms	≥One mild symptom. No moderate, marked, or severe symptoms (Symptom count=0). No moderate, marked, or severe impairment
1	No symptoms	No mild, moderate, marked, or severe symptoms. No impairment

^a^Symptom count: Sum of symptom severity, if |severity| ≥1 round up, otherwise 0. Clinical Monitoring Form symptom severity scale: none=0, mild=0.5, moderate=1, marked=1.5, and severe=2.

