#### Target Assessments

The targets selected for assessment were taking medications as prescribed, obtaining adequate sleep duration, maintaining regular routines, and managing signs and symptoms as these targets are readily amenable to monitoring using the Daily Check-In, which is a core feature of LiveWell. Medication adherence was assessed using the Tablet Routine Questionnaire [159-161] and focused on percentage adherence with prescribed psychiatric medications, not including those prescribed as needed. Sleep duration, quality, and excessive sleepiness were assessed using the CMF, QIDS, Pittsburgh Sleep Quality Index, and an additional question to capture excessive sleepiness [162-164]. Sleep duration was primarily considered in this study. Sleep quality and excessive sleepiness will be explored secondarily because interepisode insomnia and hypersomnia are risk factors for relapse [107,163,165,166]. Routine was assessed using a 5-question trait version of the Social Rhythm Metric [167-170] and will be assessed primarily by a frequency score (Multimedia Appendix 7). Finally, the management of residual and prodromal signs and symptoms was assessed using the Symptom Management Scale. This scale was developed from the prodromes coping interview and inventory, which has been used in face-to-face cognitive behavioral therapy for bipolar disorder [99,137,142,171]. The outcome measure will be the total coping score (Multimedia Appendix 7).

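### Aim 2 does not require a behavioral target to be measured before relapse, so targets changed by relapse could be reported as explaining it; for sleep only, the target also overlaps with the severity score

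*Protocol article*

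**What the plan says.** Under Aim 2: Target Analysis, a cited mediation framework will be used "to identify the targets that mediate the effect of the intervention on time to relapse, percentage time symptomatic, and symptom severity". The only other model named there for the targets is this: "Generalized linear mixed models will be used to examine the effects of time, risk strata, and study arm on longitudinal target and determinant data". Neither sentence says which target assessments enter the relapse analysis, and neither orders or lags them.

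The hypotheses in the Intervention Evaluation Overview are directional. H2 expects that "variation in the proximal behavioral targets will account for substantial variance in the (H2) primary clinical outcome (time to relapse"), with H3 and H4 making the same claim for percentage time symptomatic and symptom severity. H5 expects that "proximal behavioral targets will mediate the intervention effect on the (H5) primary clinical outcome (time to relapse"), with H6 and H7 again for the other two outcomes.

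On timing, blinded assessors "conducted outcome and target assessments by telephone at baseline and then every 8 weeks until study exit at week 48". Follow-up therefore ends at study exit, not at relapse. The Analysis Overview fits this: "Percentage time symptomatic will be calculated based only on the observed time in the study".

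On instruments, Target Assessments states: "Sleep duration, quality, and excessive sleepiness were assessed using the CMF, QIDS, Pittsburgh Sleep Quality Index". Outcome Assessments states: "Symptom severity was assessed using the Quick Inventory of Depressive Symptomatology (QIDS)–Clinician Rating and the Young Mania Rating Scale". The CMF also supplies, with the LIFE, the weekly ratings that define relapse. The other three targets have their own primary instruments: the Tablet Routine Questionnaire, the Social Rhythm Metric and the Symptom Management Scale.

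The Intervention Framework section calls the linear picture a simplification and describes outcomes, targets and determinants as acting on one another in both directions.

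**The concern.** To say that a target accounts for or mediates relapse, its value must have been set before the relapse. A value recorded afterwards may be a consequence. The article's own framework allows for that, and its Discussion says that sensed behaviors, sleep duration among them, may vary with clinical status. If post-relapse values enter the predictor, a target with no influence on relapse can appear to explain it.

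The sleep target has a second problem that timing alone does not cover. Sleep and symptom severity are both rated with the QIDS, through combined instruments, on the same call and over the same prior 2 weeks. Part of any correlation between them is the same information counted twice.

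Aim 1 is unaffected. At stake is the secondary goal of learning how the intervention works.

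**Working it through.** **Inputs.** From Sample Size Considerations: 200 participants at 2:3 (80 control, 120 LiveWell), control relapse 60% at 12 months, hazard ratio 0.61, LiveWell relapse 43%. From the assessment schedule: follow-up visits at weeks 8, 16, 24, 32, 40 and 48. The plan gives no figure for Aim 2 mediation.

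**Plan's own figure.** 1 − (1 − 0.60)^0.61 = 0.428, so the 43% reproduces.

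**Share of target assessments after first relapse.** Assume exponential relapse and full attendance. Weekly hazards are −ln(0.4)/52 = 0.0176 (control) and 0.61 × 0.0176 = 0.0107 (LiveWell). The share relapsed by week w is 1 − exp(−hazard × w).

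| Week | 8 | 16 | 24 | 32 | 40 | 48 | Mean |
|---|---|---|---|---|---|---|---|
| Control | 0.13 | 0.25 | 0.34 | 0.43 | 0.51 | 0.57 | 0.37 |
| LiveWell | 0.08 | 0.16 | 0.23 | 0.29 | 0.35 | 0.40 | 0.25 |

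Overall: (80 × 0.372 + 120 × 0.252)/200 = 0.30.

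**Simulation under a true null.** 300 trials per setting, 80/120 participants, 48 weeks. The target has no effect on relapse and the arm has no effect on the target. Target values have unit variance and within-person correlation 0.5. Relapse lowers the target by an assumed amount, either through week 48 or for 16 weeks. Two Cox models are compared, both including arm: one uses the mean of all six visits, the other the last value before each 8-week risk interval (from week 8 on). False mediation means that the arm-to-target and target-to-relapse tests are both significant at 5%.

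| Shift (SD) | Duration | Mean of all visits | Lagged value | False mediation |
|---|---|---|---|---|
| 0 | to week 48 | 7% | 4% | 0% |
| 0.25 | to week 48 | 38% | 6% | 3% |
| 0.5 | to week 48 | 87% | 6% | 5% |
| 0.8 | to week 48 | 99.7% | 5% | 14% |
| 0 | 16 weeks | 8% | 5% | 0.3% |
| 0.25 | 16 weeks | 10% | 5% | 0% |
| 0.5 | 16 weeks | 31% | 9% | 2% |
| 0.8 | 16 weeks | 60% | 3% | 3% |

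With 300 trials, the simulation standard error near 5% is √(0.05 × 0.95/300) = 1.3 percentage points. The 10% for a small, short shift is therefore not distinguishable from the 8% with no shift; the other non-zero settings are clearly inflated. Adjusting for the averaged target attenuated the log hazard ratio for arm by at most about 6%.

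**Sleep overlap.** No size can be computed, because the scoring is in an appendix that is not shown. Side by side, the two instrument statements put the QIDS in both the sleep target and the severity outcome. The overlap is smaller if the sleep score rests mainly on another source for duration, but the QIDS total would still contain sleep items rated in the same interview.

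**The case against.** The best defence is that this is an omission in a condensed article. Mediation gets one sentence and a cited framework, and windows and lags are commonly left to a full protocol or analysis plan, neither of which is shown. The authors acknowledge reciprocity, and 8-weekly targets with weekly clinical status already allow a lagged analysis. This stands in part: a reader might infer that post-relapse values will be used and that relapse effects would be reported as causes. The article does not say so; only "could" is supported.

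A reader might also infer that all four targets share instruments with the outcomes. They do not. Item sharing applies to sleep, and symptom management is asked through imagined scenarios. For relapse even the sleep overlap is limited, since an episode needs a mood entry criterion plus several moderate symptoms, so a sleep item alone cannot create one.

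A third tempting reading is that H2 to H7 would all be falsely confirmed. The simulation does not show this. The large rates are for association (H2). False mediation (H5) was far smaller, and the other hypotheses were not simulated. Percentage time symptomatic and severity span all of follow-up, so their difficulty is concurrent measurement, not measurement after relapse.

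Finally, the shift sizes, the within-person correlation and the averaged predictor are assumptions, and persistence of the shift matters a great deal.

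What the defence does not remove: the stated hypotheses give targets an explanatory role with no ordering rule, against the article's own account of two-way influence, and the sleep-severity overlap is fixed by the stated instruments.

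**Conclusion.** The point holds in a limited form. About 30% of follow-up target assessments would come after first relapse on the plan's rates, assuming exponential relapse and full attendance. If all visits are used, H2 is exposed for any target that relapse can change: a false association in about 10 to 38% of trials at 0.25 SD and 31 to 87% at 0.5 SD, from a 16-week to a persistent shift, against 3 to 9% with lagged values. The documents give no shift size, so these are ranges, not predictions.

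False mediation (H5) was 0 to 14%, but only with no effect of LiveWell on the target. If LiveWell does change the target, as Aim 2 H1 supposes, this rate could move toward the H2 rate; that case was not calculated.

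Separately, for sleep only, the relations with symptom severity (H4, H7) are partly built in. The change is worth making because it is cheap and uses data already collected. The primary result does not depend on it.

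**What to change.** - **Relapse analyses (H2, H5):** fit a Cox model with each target as a time-varying covariate, lagged to the last assessment before the at-risk week, using the baseline value before week 8. Lag by the actual assessment date, since visits may be completed up to 4 weeks late.
- **Percentage time symptomatic and severity (H3, H4, H6, H7):** use target values measured before the outcome window.
- **Sleep as predictor or mediator:** score severity without its sleep items, at least as a sensitivity analysis.
- **Week-16 landmark:** sensitivity analysis only. It removes about 25% of control and 16% of LiveWell participants (80 × 0.246 + 120 × 0.158 = 39 of 200) and conditions on a post-randomization event expected to differ by arm.

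No new data are needed, only somewhat more analysis work. The modified severity score is not directly comparable with the published total. A baseline value cannot carry an intervention effect, so mediation is not visible for relapses before week 8 (80 × 0.13 + 120 × 0.08 = about 20 participants). Lagging also does not remove prodromal symptoms that alter a target before episode criteria are met, so the results should still be worded as associations consistent with mediation.
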